### Sensitivity analysis

Primary analyses assume the missing data are missing at random (MAR). It is thus important to assess the sensitivity of analysis under the MAR assumption to the not missing at random (NMAR) assumption. We will investigate various scenarios of non-ignorable missing data mechanisms through a sensitivity analysis based on a mixture modelling approach. Missing data will be imputed under MAR assumption first, and parameter estimates for each imputed data set will be obtained [20].

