### Participants and research eligibility

The primary hypothesis will be tested using a longitudinal school survey. Three waves of data will be collected; pre-intervention (baseline), and two waves post-intervention (see Fig. 1, Flow diagram).

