### Statistical analyses

Intention-to-treat analyses will be employed. To account for within-individual variation we will employ repeated measures models with split-plot in time design matrix with binary outcome and logit link. Model parameters will be estimated using generalised estimating equations (GEEs) accounting for correlation within participants with an exchangeable working correlation matrix. For continuous secondary outcomes, GEEs with a Gaussian distribution and identity link will be implemented.

To assess the impact of the intervention on primary and secondary outcomes, time by treatment interactions will be examined in a model that includes the fixed categorical effects of assessment time, group indicator and treatment by group interaction. Trend effects due to staggered rollout of the intervention will be assed using models with a fixed effect categorical factor for year of treatment.

Clustering effects for schools and communities will be evaluated by calculating ICC and, if necessary, a series of (generalised) linear mixed models accounting for *clustering* (within participant/class/school/community). Analysts will not be blind to the communities that have been allocated to either intervention or control.

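### The primary analysis is said to assume MAR, but the GEE that is specified is in general consistent only under MCAR given its covariates; the MAR imputation is described only as a sensitivity-analysis step

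*Protocol article*

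**What the plan says.** Under Statistical analyses the protocol article chooses "repeated measures models with split-plot in time design matrix with binary outcome and logit link" and continues: "Model parameters will be estimated using generalised estimating equations (GEEs) accounting for correlation within participants with an exchangeable working correlation matrix". The treatment effect comes from "a model that includes the fixed categorical effects of assessment time, group indicator and treatment by group interaction" (I read the last term as time by group, since the same sentence announces time by treatment interactions). No weights, imputation or further covariates are named for this model. Mixed models appear in the same section, but conditionally and for clustering: "if necessary, a series of (generalised) linear mixed models accounting for" clustering.

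Under Sensitivity analysis the article says "Primary analyses assume the missing data are missing at random (MAR". It then turns to departures from that assumption: "We will investigate various scenarios of non-ignorable missing data mechanisms through a sensitivity analysis based on a mixture modelling approach". The imputation sentence follows directly: "Missing data will be imputed under MAR assumption first, and parameter estimates for each imputed data set will be obtained".

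Under Participants and research eligibility: "Three waves of data will be collected; pre-intervention (baseline), and two waves post-intervention". Under Sample size, 80% retention is assumed.

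**The concern.** MAR is enough for a correctly specified likelihood analysis, for multiple imputation with a suitable model, and for correctly weighted GEE. It is not enough in general for an ordinary GEE on the records that happen to be available. The article therefore credits its primary estimator with a property that the estimator, as described, does not have.

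Two consequences follow. First, the plan measures school commitment, attendance and tobacco use, which plausibly predict both dropout and drinking. The primary model cannot use any of them. Second, the NMAR scenarios would depart from an imputation-based MAR estimate that is not the primary estimate. A shift between the primary result and an NMAR result would then mix a change of method (GEE to imputation) with a change of assumption (MAR to NMAR).

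**Working it through.** **1. Amount of missing data.** From Sample size: 3,500 × 0.80 = 2,800, which reproduces the stated figure. The planned loss is 3,500 − 2,800 = 700 students, or 20%.

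**2. What the estimator needs.** The GEE solves Σ D′V⁻¹(y − μ) = 0 over the observed records. This has mean zero if, within each arm and wave, the students still observed have mean outcome μ. That holds when missingness is unrelated to outcomes or depends only on arm and wave. If dropout depends on earlier drinking (MAR), it fails in general. When the exchangeable working correlation is close to the truth, the earlier waves recover most of the deficit, so the size has to be computed.

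**3. Dropout driven by earlier drinking.** Assumptions not in the document: control prevalence 35/45/55% over the waves; a 15% relative reduction, so wave 3 is 55.00% versus 46.75%; latent correlation exchangeable 0.6 or AR(1) 0.7; monotone dropout depending on the previous wave's outcome.

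True difference: 46.75 − 55.00 = −8.25 points. True log OR: ln(0.4675/0.5325) − ln(0.55/0.45) = −0.331, OR 0.718.

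Large-sample limits of the GEE at wave 3 (dropout OR is for prior drinkers):

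| Scenario | Control | Intervention | Difference (points) | Shift (points) | Log-OR bias | OR |
|---|---|---|---|---|---|---|
| MCAR | 0.5500 | 0.4675 | −8.25 | 0 | 0 | 0.718 |
| 20% loss, exchangeable, dropout OR 3 in both arms | 0.5495 | 0.4666 | −8.29 | −0.04 | −0.0013 | 0.717 |
| 20% loss, AR, OR 3 in both arms | 0.5513 | 0.4688 | −8.25 | 0.00 | −0.0002 | 0.718 |
| 20% loss, AR, OR 3 in control only | 0.5517 | 0.4675 | −8.42 | −0.17 | −0.0071 | 0.713 |
| 20% loss, AR, OR 3 in control, 1/3 in intervention | 0.5521 | 0.4657 | −8.64 | −0.39 | −0.0158 | 0.707 |
| 40% loss (assumed), AR, OR 3 versus 1/3 | 0.5548 | 0.4627 | −9.21 | −0.96 | −0.0386 | 0.691 |

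A rough standard error, ignoring clustering and using wave 3 only with 1,400 per arm, is √[1/(1,400 × 0.55 × 0.45) + 1/(1,400 × 0.4675 × 0.5325)] = 0.076. The worst 20% case is 0.0158/0.076, about a fifth of that.

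A separate simulation used prevalence 35/50/60%. In the intervention arm 65% of baseline drinkers and 88% of non-drinkers were retained (0.35 × 0.65 + 0.65 × 0.88 = 0.80); in control 80% were retained regardless. The raw available-case difference moved by about 2.4 points and the GEE by 0.2. A second design, with dropout by previous-wave use and decaying correlation, gave GEE shifts of 0.1 to 0.3.

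**4. Dropout driven by a recorded variable outside the model.** Assumptions: the same 35/45/55% and 15% effect; a risk factor marking the top 30% of students; retention 60% among them and 89% among the rest. Overall retention is 0.30 × 0.60 + 0.70 × 0.89 = 0.18 + 0.623 = 0.803. The high-risk share among those retained is 0.18/0.803 = 22.4%, down 7.6 points from 30%. For every 10-point gap in drinking between high-risk and other students, observed prevalence in that arm falls by 0.76 points before the GEE borrows from earlier waves.

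- Same pattern in both arms: shift about 0.2 points or less, within simulation noise.
- Pattern in one arm only, or reversed between arms: shift of 0.7 to 1.4 points (log OR 0.03 to 0.055).
- A second calculation with another assumed driver: almost no shift when the arms were alike, and about 2 to 3 points when the pattern differed by arm.

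Against 8.25 points, 0.7 is 8% and 3 is 36%. The direction depends on which arm loses the high-risk students.

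**The case against.** The strongest reply has four parts.

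*The plan is silent rather than wrong.* The article never says that the GEE is unweighted or run on available records only, and a fuller analysis plan could add weights or imputation. This is fair, and a reader should not infer that an uncorrected available-case analysis has been fixed. But the article states both an estimator and an assumption, and the two do not match as written. That is more than a detail left for later.

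*The imputation may already be primary.* The section opens with the primary analyses, and imputing under MAR first could mean that the GEE is fitted to each imputed set. The wording allows this. However, the sentence stands under Sensitivity analysis, directly after the NMAR mixture approach, and the primary model is described elsewhere without it. If this is the intention, one sentence settles the matter.

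*The mixed models give a likelihood route.* They would be valid under MAR if correctly specified, but they are conditional on the ICC evaluation and offered for clustering. They would also omit the same auxiliary variables, so that exposure is not peculiar to GEE. This part stands.

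*The bias is negligible.* For dropout driven by earlier drinking at 20% loss this is right. A reader might take the shift of about 2.4 points in the raw difference as the error of the primary analysis. It is not: the plan does not use the raw difference, and the GEE recovers nearly all of that shift.

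**Conclusion.** The mismatch stands: the stated assumption is MAR, and the estimator as described needs, in general, MCAR given time and group. The remedy that would supply MAR validity is described only as a sensitivity step.

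The size is modest. At 20% loss with dropout depending on earlier drinking, the shift was 0.3 points or less in simulation and 0.39 points (0.016 in log OR) in the worst exact case. It was also small in the scenarios at 20% loss where both arms dropped out alike. Roughly 1 to 3 points arises only under assumed arm-differential dropout driven by recorded variables outside the model.

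A reader might infer that the primary result will be materially biased. The documents do not support that. They give no dropout pattern by arm and do not show that leavers drink more. What they show is a possible route: the Fig. 1 legend has the final wave including students one year post school, while Sample size and Survey measures place primary outcome collection in the school setting. The prevalences, correlations and dropout patterns used above are all assumptions. The point deserves correction because it is cheap and because the analysts will not be blind to allocation, so the choice is best settled before outcome data are analysed.

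**What to change.** Preferred: make the MAR imputation already planned the basis of the primary analysis. Fit the primary GEE to each imputed data set and pool the estimates. Put prior alcohol use and recorded predictors of dropout (for example school commitment, attendance and tobacco use) in the imputation model. Start the NMAR scenarios from that same MAR estimate, so that any shift reflects the change of assumption alone.

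Alternative: use inverse-probability-weighted GEE, with the same variables in the model for remaining in the study, and anchor the NMAR scenarios to that estimate.

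Minimum: leave the GEE as it is and restate the assumption under Sensitivity analysis, saying that the primary GEE assumes MCAR given the covariates in the model and that the MAR imputation is a separate, supporting analysis.

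If the imputation was always meant to feed the primary estimate, say so under Statistical analyses.

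Cost: a little more analysis and computing, and reliance on an imputation or weighting model that must itself be reasonable. The sample size is unaffected, and the auxiliary variables named are already collected.

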### Secondary outcome analyses

Per-protocol and subgroup analyses will be performed. Depending on sample size, subgroup analyses will examine differential effects by age, gender, community, rural areas, socio-economic status, State, and the extent of implementation and fidelity to the CTC process. Using (generalised) structural equation models, analysis of whether effects intervention processes on multiple outcomes (e.g. alcohol and drug use; violence; school completion) are mediated by changes in patterns of adolescent alcohol use will be assessed, after adjusting for other risk factors. Specified intervention mechanisms examined will include: percentage of outlets selling alcohol to perceived minors, reported exposure to brief communication resources; reduced perceptions of alcohol availability from different sources; and less favourable peer, family and community attitudes to alcohol. In addition, individual-level mediation analyses will be used to explore how any observed intervention effects on knowledge, attitudes, intention and skills account for any observed differences in reported alcohol consumption over the last 30 days.

### Economic evaluation

The economic evaluation will include both a trial-based analysis (i.e. costs and outcomes exactly as per the trial period) and a modelled analysis that will estimate the longer term economic benefits for the community. This will include cost-effectiveness, cost-utility, cost-benefit and cost-consequences analyses. It is expected that the CTC intervention will:Result in substantial economic benefits relative to the control communities related to reductions in each of the following:Alcohol use problems and harms, illicit drug use and tobacco smoking;Alcohol-related hospital admissions (specifically alcohol-related emergency department admissions);Alcohol-related violence and other offending; andFailure to complete secondary school.b.Deliver an attractive internal rate of return (IRR) with economic returns well above intervention costs from a societal perspective;c.Be cost-effective from a health sector perspective, with the relationship between health gains and net cost well below the decision threshold commonly used in Australia (<$50,000 per Quality-adjusted life year (QALY)).

Trial outcomes will be promoted in peer-review publications and community fora.

### Registration, ethics and data management

The Trial is registered with the Australian and New Zealand Clinical Trial Registry (http://www.anzctr.org.au/; ACTRN12616001276448). The trial team started to develop relationships with community stakeholders in January, 2016, in order to build community capacity to implement the CTC framework. As community relationships were initiated, in September, 2016, the trial was retrospectively registered. The first wave of the trial and longitudinal data was collected in February, 2017.

There are no predetermined criteria for discontinuing or modifying the trial. No anticipated adverse consequences are anticipated for trial participants. In the case of any occurrence, details will be forwarded to Deakin University’s Human Research ethics committee, in accordance with the conditions of the ethics approval for the project. The current protocol (version 1) is in keeping with the current ethics approval. Any protocol modification will be, where appropriate, referred to Deakin University’s Human Research Ethics Committee and communicated through the trial registration listed in the Australian New Zealand Clinical Trials Registry.

Data management will be primarily the responsibility of the research team based at the School of Psychology, Deakin University. Management of trial data will be in accordance with a data-management protocol, which has been developed and approved by the Project Advisory Group, and available on request. The study protocol details requirements regarding data entry, data cleaning, data back-up, secure storage and transport, and analysis. The Deakin University Human Research Ethics Committee (DUHREC) has approved the project with the expectation that data will be securely stored, and accessible only to primary researchers and statisticians through allocation of access rights. Ethics approval number from DUHREC is 2,015,261.

Confidential data on school and community contact details (e.g. phone numbers, email addresses) will be stored in a secure dataset that is not linked to survey response datasets. A trained research manager will be the only person with access to confidential participant data. The National Health and Medical Research Council (NHMRC) is the primary funder of the trial (see https://www.nhmrc.gov.au/). The NHMRC will have no role in the implementation or management of the intervention, collection, management, analysis or interpretation or the publication of the trial data.

## Discussion

The Communities that Care intervention approach has been found to be effective in the USA [2, 4–6]. This trail will test its potential to reduce alcohol use among teenagers in Australia. We expect that the present approach will be associated with significant effects on alcohol use amongst adolescents because interventions adopted within communities will be based on evidence-based practices and target specific problems identified from surveys conducted within each community [2, 3]. The present study ascribes an important role to coalitions in the management and monitoring and sustainability of interventions.

## Abbreviations

AUDIT: Alcohol Use Disorders Identification Test
CTC: Communities That Care
DUHREC: Deakin University Human Research Ethics Committee
GEE: Generalised estimating eqs.
ICC: Intraclass correlation coefficients
IRR: Internal rate of return.
MAR: Missing at random
NAPLAN: National Assessment Program – Literacy and Numeracy
NHMRC: National Health and Medical Research Council
QALY: Quality-adjusted life year
SEIFA: Socio-Economic Indexes for Areas
SES: Socioeconomic status
SLA: Statistical Local Areas
SMFQ: Short mood and feeling questionnaire
USA: United States of America
